### Interventions

#### Control group

Eligible participants who are assigned to the control group will receive basic treatment, including daily rehabilitation training and clinical medications. Conventional rehabilitation therapies include physical therapy (PT) and occupational therapy (OT). The PT mainly includes functional training, modality, and manual therapy. The OT mainly includes upper limb function training. Those therapies above are the trained therapist based on the participants’ dysfunctional situation to choose the corresponding rehabilitation training, which is to promote upper limb motor function recovery as the main purpose. Specifically, all participants will not receive Tai Chi treatments during the intervention. And therapists are required to track and record specific rehabilitation programs and accurate information such as the frequency and the duration of each intervention and the standard CRTs for 40 min per day, 6 days per week, for 3 weeks.

#### Intervention group

The participants in the intervention group will also accept CRTs, which are identical to the control group. The difference between the two groups is that the intervention group will perform TCY-MIT for 30 min per day, 6 days per week, for 3 weeks. The TCY-MIT consists of 4 steps, and the process is as follows.
Step 1: Participants will be organized to watch a video of the TCY exercise movement. The trained TCY therapists will demonstrate the movement of A to F (Fig. 3) and teach the participants to perform TCY exercise with their affected upper limb.Step 2: Participants will wear headphones and relax by listening to soft music for 4 min.Step 3: Participants will undergo 24 min of imagining the TCY exercise with instructions. Participants will be asked to apply kinesthetic images (first-person images) related to using the affected upper limb.Step 4: In the final 2 min, participants will be allowed to refocus on the room.

**Fig. 3 Fig3:**
[figure not shown]
All the movements of Tai Chi Yunshou exercise. The movement of A to F show that how to perform Tai Chi Yunshou exercise

All TCY-MIT will be administered by a trained occupational therapist. The therapist will check for actual movement and intermittently ask participants to describe what they are doing and what they are experiencing to maintain compliance [16].

### Outcome measures and follow-up

Outcome measures will be performed by a certified, trained occupational therapist who is blinded to the group allocation of the participants. The assessments will be administered at baseline, after completion of the intervention (1, 2, and 3 weeks), and at the end of follow-up (2 months). Furthermore, resting-state fNIRS signal data collection will be a trained fNIRS technician.

### Primary outcome measure

#### Motor function

The primary outcome measure is a change in score on the Fugl-Meyer Assessment of Upper Extremity (FMA-UE). The FMA-UE has been used to assess MIT-induced changes in upper extremity motor impairment in numerous RCTs [17, 18]. The acquired data are in the form of a 3-point ordinal scale (0 = cannot perform at all; 1 = can perform partially; 2 = can perform fully) that is calculated for each item [16]. The scale contains a total of 33 items, which are summed to provide the maximum score of 66. Assessors evaluated all participants immediately before therapy, after 3 weeks of therapy, and at the end of follow-up.

### Secondary outcome measures

The secondary outcome measures are changes in Box and Block Test (BBT), Muscle strength test (MST), modified Barthel index (MBI), and Pearson correlation coefficients (r) from baseline to postintervention follow-up.

#### Manual dexterity

The BBT measures gross manual dexterity in poststroke patients [6]. It consists of a box divided by a partition into two equal-sized compartments and 150 pieces 2.5 cm square of wooden blocks. The participants are requested to use their hemiplegic hands to move the maximum number of wooden blocks without other assistance, and the number of blocks carried from one compartment to the other within 60 s is used as the test score. The participants will be required to repeat the test twice with each hand. After evaluation, the assessor counts the score and takes the average of the two trials as the final score.

#### Muscle strength testing

The computer-assisted (Biometrics Ltd, E-Link) muscle strength test includes hand grip and pinch (thumb and forefinger) strength. Each participant will be asked to grip and pinch the dynamometer with maximal press power. Before this test, the evaluator asks participants if they are ready. Then, the “Go” instruction is given for the participant to start this test. To improve the reliability of muscle strength measurement, participants repeat this test on each hand three times. To minimize deviations and disturbances caused by participants, all participants will not be able to know their MST results during the test (face away from the computer). The examiner counts the score and takes the maximal press power of the three trials as the final score.

#### Activities of daily living

The MBI is a functional outcome measure of activities of daily living (ADL) that includes 10 items; it has satisfactory reliability and validity in poststroke patients. Ten functional activities will be evaluated: feeding, bowel control, bladder control, personal hygiene, transfer, dressing, toileting, ambulation, bathing, and stair climbing. The MBI evaluates global disability by measuring the level of the ADL with a score from 0 (complete dependence) to 100 (full independence).

#### Pearson’s correlation coefficient

Brain network connection analysis has been widely used in the assessment of impaired brain function [19]. fNIRS is a novel, noninvasive brain function imaging technology to detect changes in oxygenated haemoglobin and deoxygenated haemoglobin in the cerebral cortex in a timely manner [20]. fNIRS will be applied to record resting-state signals with two groups. Brain functional connectivity will be calculated, and graph theoretical analysis will be further applied to represent topological relationships in complex brain networks (Fig. 4).

**Fig. 4 Fig4:**
[figure not shown]
The graph theoretical analysis process of fNIRS-brain networks. **A** Schematic illustration of the fNIRS channels layout. **B** fNIRS-Blood oxygen signals. **C** Construct a N × N correlation matrix. **D** Set threshold to construct a new correlation matrix. **E** Brain functional connectivity

In this study, we will use a multichannel fNIRS system (NirSmart-II, HuiChuang, China) with two wavelengths (730 nm and 850 nm) at a sampling rate of 11 Hz. The NirSpark software (v1.7.3) package will be used to preprocess fNIRS signal data and construct brain functional networks. We will explore the structural characteristics of the resting brain network in poststroke patients and assess differences between the two groups. Resting-state fNIRS data will be collected for 10 min to subsequently construct brain functional networks. Pearson correlation of oxygenated haemoglobin on time series of each channel and brain region will be calculated, and Pearson’s correlation coefficient (r) is defined as the resting-state functional connection of corresponding channels and brain region strength.

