### Statistical analysis

A sample size of 64 participants (32 per group) was determined to provide 90% power (*α* 0·05) to detect a mean FMA-UE difference of 11.0 (SD 9) points between the two treatment groups. The main analysis of this trial consists of a comparison of the outcomes after 3 weeks and at the end of follow-up (2 months). The statistician who is blinded to the group allocation of the participants will lock all data before statistical analysis. All data will be analysed with Social Sciences (SPSS) version 26.0 software (IBM Corporation, Armonk, USA) and GraphPad Prism version 9.0 software (GraphPad Software Inc., San Diego, USA). The baseline data and outcome analyses will be conducted on the full analysis set (FAS), using intent-to-treat (ITT) samples and completer samples. The per protocol set (PPS) will be used to analyse effective cases based on FAS. Furthermore, safety analysis will be performed on safety assessment set (SAS). Demographic data will be analysed using a two-sample *t*-test or Wilcoxon rank-sum test for continuous variables and the chi-squared test or Fisher’s exact test for categorical variables. For outcome, variables will be presented as the mean ± standard deviation ($$ \overline{x}\pm \mathrm{s} $$). Primary outcomes and secondary outcomes will be analysed using multivariable analysis of variance (ANOVA) for repeated measures, followed by Tukey's post hoc test. Statistical significance will be set at a *P value* less than 0.05.

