Our study has several strengths. (1) the design and report of the trial protocol strictly follow the SPIRIT statement, and this study will adhere to CONSORT 2010. (2) The TCY exercise is a household name, group training program. It is easy to conduct TCY-MIT in the stroke population and to improve the participants’ compliance. (3) Few studies have examined neural activity during TCY-MIT. We will capture cerebral cortex blood oxygen changes during neural activities to reveal the potential mechanisms of TCY-MIT combined with CRTs via fNIRS-based resting-state brain network analysis. We hypothesized that compared with the control group, participants in the intervention group will show increased brain functional connectivity and that the *r* value is related to the primary outcome. The fNIRS technician (blinded to the group allocation of the participants) will be assigned to take charge of fNIRS-based resting-state data collection and analysis. (4) In this trial, we are not only focusing on the recovery of motor function after the intervention, but we are also using the MBI score as an outcome measure to assess ADL in poststroke patients after completion of the interventions (3 weeks) and at the 6-month postintervention follow-up (2 months).

However, there are a few limitations. First, the intervention time for stroke patients is only 3 weeks due to the duration limit of hospitalization that is set for the patients. Second, this is a single-centre study. A multicentre, larger sample size is required to prove our objectives. Third, it is difficult to objectively monitor whether the participants are engaging in TCY-MIT rather than other mental activities. Fourth, the study does not use fNIRS to perform analysis of cortical activation with tasks.

In summary, the results of the study will be beneficial to optimize rehabilitation training methods and provide new therapeutic ideas for stroke rehabilitation. Our team will further explore the individualized rehabilitation program of TCY-MIT in future work.

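### The connectivity outcome is a set of r values with no named endpoint, and the stated test at P < 0.05 does not correct across connections

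*Protocol article*

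**What the plan says.** All references are to the protocol article.

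- **Secondary outcome measures** lists, with the dexterity and strength tests, changes in "modified Barthel index (MBI), and Pearson correlation coefficients (r) from baseline to postintervention follow-up".
- **Pearson's correlation coefficient**, with the Fig. 4 legend, shows how r arises. One step is "Construct a N × N correlation matrix", followed by a thresholded matrix and a network. The text adds that "Pearson correlation of oxygenated haemoglobin on time series of each channel and brain region will be calculated", and that the study will "assess differences between the two groups". It names no connection, region pair or summary measure for that comparison.
- **Statistical analysis** states: "Primary outcomes and secondary outcomes will be analysed using multivariable analysis of variance (ANOVA) for repeated measures, followed by Tukey's post hoc test". It then says: "Statistical significance will be set at a *P value* less than 0.05". The main comparisons are at 3 weeks and 2 months.
- **Discussion** (strengths) hypothesises that, relative to control, "participants in the intervention group will show increased brain functional connectivity", and that r is related to the primary outcome. The end of the Background expects more effective connections within damaged areas, or between damaged and normal areas.

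**The concern.** The other secondary measures give one or a few scores per patient. Connectivity gives as many as there are pairs of channels, and a further set at region level. The article fixes a test, a post hoc procedure and a threshold for this outcome, but the post hoc procedure covers a different family. Tukey's test adjusts comparisons of means within one ANOVA, that is, for one r. With two arms there is only one between-group pair at a given visit, and nothing carries over from one connection to the next.

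The hypothesis is directional but names no pair, and it accepts more than one type of connection. A significant increase in any of many places could therefore be read as confirmation. fNIRS connectivity is the trial's only stated secondary objective and the basis of its mechanism claim, so the interpretation of that claim is what is at stake.

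**Working it through.** **Inputs from the article.** Threshold 0.05; two arms at 1:1; 32 evaluable patients per group; r values taken from an N × N matrix. The sample-size section specifies a two-tailed test. Two-sided testing is assumed here too, so each test has a nominal 2.5% chance of a false increase.

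**The plan's own figure.** The article states no error rate for connectivity. Its one calculated figure, the sample size, reproduces: (1.96 + 1.28)² × 9² × 2 / (47 − 36 − 3.6)² = 10.4976 × 162 / 54.76 = 31.06, which rounds up to 32 per group. That group size is used below.

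**Inputs assumed.** N is not in the text and the channel layout figure is not shown, so N = 4 (a few regions) to N = 35 (many channels) is used. Correlation between connections is not given either; 0, 0.5 and 0.8 are used. Each r is assumed to be tested separately, once, with no true effect.

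**Formulas.**
- Distinct r values: m = N(N − 1)/2.
- Expected false positives: 0.05 × m, whatever the correlation.
- Independent tests: P(any false positive) = 1 − 0.95^m; P(any false increase) = 1 − 0.975^m.
- Correlated tests: null simulation of 1,000 trials per setting, 32 per arm, a t-test on each connection, equal correlation between connections.

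**Worked example, N = 4.** m = 4 × 3/2 = 6; expected false positives 0.05 × 6 = 0.3; 1 − 0.95⁶ = 26.5%; 1 − 0.975⁶ = 14.1%.

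**Results** (any false positive / any false increase):

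| N | m | Expected false positives | Independent | Correlation 0.5 | Correlation 0.8 |
|---|---|---|---|---|---|
| 4 | 6 | 0.3 | 26.5% / 14.1% | 21.7% / 12.0% | 14.0% / 7.7% |
| 8 | 28 | 1.4 | 76.2% / 50.8% | 51.8% / 23.8% | 23.5% / 12.5% |
| 20 | 190 | 9.5 | 99.99% / 99.2% | 90.5% / 48.7% | 41.7% / 21.3% |
| 35 | 595 | 29.75 | about 100% / about 100% | 99.3% / 62.4% | 53.4% / 26.3% |

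Every setting exceeds the nominal 5% and 2.5%. The smallest chance of a false increase is 7.7%, with 6 values at correlation 0.8. The simulation uses a single t-test per connection in place of the repeated-measures ANOVA. It covers one visit and one level, so a second visit, the other level (channel or region) and graph measures would add further tests.

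**The case against.** The strongest objection is that separate testing of every connection is an inference. The article says that r is calculated, arranged in a matrix, thresholded and turned into a network, and that the groups will be compared. It does not say that each pair is tested. The Discussion refers to the r value in the singular, and the hypothesis of more effective connections can be read at network level. One summary per patient would largely remove the problem. This stands, and the conclusion is therefore conditional. On the other side, the outcome list uses the plural, r is defined per channel and region, and no summary is named.

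A second objection is that endpoint detail and multiplicity handling for imaging are often left to an analysis plan, and that a general 0.05 level does not exclude adjusted P values. This stands in part. But the article does more than stay silent: it specifies a procedure for this outcome, and that procedure does not fit an outcome made up of many r values.

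Third, the article uses exploratory language for the network analysis. That is true, but it also states directional connectivity hypotheses.

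A reader might also infer that the plan commits to hundreds of uncorrected tests, or that any connectivity finding would be worthless. The documents support neither. N is unknown and may be small at region level, and Tukey's test is specified, although for another family. A broad, consistent shift across connections would still be informative; an isolated significant pair is what would be weak.

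**Conclusion.** The point holds in conditional form. The rule stated for secondary outcomes does not control error across connections, and no connectivity endpoint is named to make such control unnecessary. If connections are tested individually, the chance of at least one falsely significant increase is above 2.5% in every setting examined. It is about 14% with 6 independent values; with 190 values it is about 49% at correlation 0.5 and 21% at correlation 0.8. These figures rest on assumed N, assumed equal correlation, separate tests and one comparison per connection. That a false increase is more likely than not cannot be claimed in general: it is so for independent tests from about N = 8, but at correlation 0.8 it is not so even with 595 values.

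The consequence is limited to the mechanism hypothesis, for which isolated significant connections would be weak support. The FMA-UE analysis and the sample size are not affected.

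**What to change.** Before the data are analysed, add to the analysis text:

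1. One connectivity summary per patient, for example mean r over a pre-listed set of region pairs, at one named visit, tested once at 0.05.
2. All other channel pairs, region pairs and graph measures reported as exploratory, with 5% false-discovery-rate control (Benjamini-Hochberg), or with a permutation maximum-statistic or network-based test.
3. A sentence saying that Tukey's test applies within one ANOVA and is not the correction across connections.

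This is a change of wording and needs no new data. The cost is that a single connection needs stronger evidence to be called significant. For scale, the strictest simple rule (Bonferroni) with 190 values would require P below 0.05/190 = 0.00026.

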To address poststroke patients’ difficulty in performing TCY exercise, this study was designed to investigate the effectiveness of TCY combined with MIT on upper extremity motor function (UE-MF) recovery in these patients. Furthermore, there is minimal brain plasticity evidence associated with this training form. Our objective was also to explore the cortical reorganization patterns after Tai Chi Yunshou motor imagery training (TCY-MIT) in stroke patients. In this study protocol, we will describe the rationale, design, and analytic methods of an RCT designed to investigate the rehabilitative effects of Tai Chi among hospitalized stroke patients in the recovery phase. We hypothesized that poststroke patients with hemiplegic upper extremities have a better treatment and response to TCY-MIT combined with conventional rehabilitation therapies (CRTs) than individuals with CRTs treatment. Meanwhile, there will be more effective connections between damaged brain areas or between normal brain areas and damaged brain areas in the TCY-MIT combined with CRTs group.

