### Sample size

The sample size was estimated based on a comparison between the intervention group and the control group, represented by the improvement of the Fugl-Meyer Assessment of Upper Extremity (FMA-UE) as the primary outcome. In this study, a two-tailed test was chosen, *α* = 0.05. *μ*_*r*_ and *μ*_*c*_ represent the mean of FMA-LE scores after treatment in the intervention group (TCY-MIT + CRTs group) and the control group (CRTs group) respectively. *K* is the ratio of the sample size between the intervention group and the control group, so *K* = 1. According to the results of previous study [14], *μ*_*r*=_47.00, *μ*_*c*_=36.00, σ = 9, Δ = 3.6, *Z*_1 − *α*_= 1.96, and *Z*_1 − *β*_= 1.28. The calculated sample size of each group was approximately 32 individuals to achieve a power of 0.90 at a significance level of 0.05. After accounting for an anticipated dropout rate of 20%, the total number of patients required for this trial was 78, with 39 in each group. The formulas are as follows:
$$ {\displaystyle \begin{array}{c}{n}_r=\mathrm{K}{n}_c\\ {}{n}_c=\frac{{\left({Z}_{1-\alpha }+{Z}_{1-\beta}\right)}^2{\sigma}^2\left(1+\frac{1}{k}\right)}{{\left({\mu}_r-{\mu}_c-\Delta \right)}^2}\end{array}} $$

where *μ*_*r*_ is the mean of the intervention group, *μ*_*c*_ is the mean of the control group, *K* is the ratio of the sample size between the intervention group and the control group, Δ is the margin of superiority, and σ is the standard deviation.

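### The fNIRS secondary outcome (Pearson r) is a matrix of values with no per-patient summary, no error control across connections and no link to the lesion that the mechanism hypothesis is about

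*Protocol article*

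**What the plan says.** Under Secondary outcome measures, the article lists changes in the Box and Block Test, muscle strength and the modified Barthel index "and Pearson correlation coefficients (r) from baseline to postintervention follow-up". So r has the same formal status as the three clinical measures.

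The text with Fig. 4 computes Pearson correlations of oxygenated haemoglobin time series by channel and by brain region, and says that r "is defined as the resting-state functional connection of corresponding channels and brain region strength". The Fig. 4 legend gives the steps "Construct a N × N correlation matrix" and then "Set threshold to construct a new correlation matrix". The fNIRS section also plans graph-theoretical analysis and names no metric.

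Under Statistical analysis: "Primary outcomes and secondary outcomes will be analysed using multivariable analysis of variance (ANOVA) for repeated measures", followed by Tukey's post hoc test, and "Statistical significance will be set at a *P value* less than 0.05". The main comparisons are at 3 weeks and at 2 months.

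The Background predicts that, in the combined-treatment group, "there will be more effective connections between damaged brain areas or between normal brain areas and damaged brain areas". The Discussion adds that connectivity will increase and that r will be related to the primary outcome.

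**The concern.** A secondary outcome needs a rule that turns the measurements into one value per patient. The article gives such a rule for the other three: the mean of two trials for the Box and Block Test, the maximum of three for strength, and a 0 to 100 total for the Barthel index. For r it gives none. Which channels, regions, summary or graph metric will represent connectivity stays open, while the 0.05 rule for all outcomes still applies to whatever is tested.

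The outcome also does not line up with the hypothesis. The hypothesis is about damaged and normal areas, but r is defined by channel and region. Eligibility requires a first stroke and right-handedness and does not restrict the side of the lesion. The same channel can therefore lie over the damaged hemisphere in one patient and over the intact one in another.

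fNIRS is the only secondary objective and carries the trial's mechanistic claim. If the quantity is chosen after the data are seen, a positive connectivity result would be weak evidence.

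**Working it through.** **The plan's own figures.** The article gives no number of tests, error rate or power for the fNIRS outcome, so there is nothing of its own to reproduce on this point. The only related figure is the sample size for the primary outcome: (1.96 + 1.28)² × 9² × 2 / (47 − 36 − 3.6)² = 31.06, rounded up to 32 per group. It reproduces, and 32 per group is used in step 3.

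**Inputs.** The threshold of 0.05 is from Statistical analysis. The two-sided test is from Sample size ("a two-tailed test was chosen", stated there for the primary outcome). The N × N matrix is from the Fig. 4 legend. N itself is not in the readable text, because the channel layout is in a figure that is not shown. It is assumed below over a range from a few regions to a dense channel array.

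**Step 1: number of distinct connections.** m = N(N−1)/2.

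**Step 2: expected false positives per comparison, if each connection is tested once with no true effect.** E = 0.05 × m. If the tests were independent, the chance of at least one is 1 − 0.95^m.

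| N (assumed) | m | E | Chance of at least one, independent tests |
|---|---|---|---|
| 4 | 6 | 0.3 | 26% |
| 6 | 15 | 0.75 | 54% |
| 8 | 28 | 1.4 | 76% |
| 16 | 120 | 6.0 | 99.8% |
| 20 | 190 | 9.5 | >99.9% |
| 35 | 595 | 29.8 | about 100% |
| 48 | 1128 | 56.4 | about 100% |

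Testing at both main time points doubles E; for N = 20 it becomes 19.0.

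**Step 3: dependence.** Connections within one brain are correlated. A simulation used 32 patients per group, one t-test per connection, a common correlation ρ between connections and 600 runs.

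| N | ρ | Mean false positives | Chance of at least one |
|---|---|---|---|
| 8 | 0.3 | 1.36 | 62% |
| 8 | 0.5 | 1.32 | 49% |
| 8 | 0.8 | 1.18 | 23% |
| 20 | 0.3 | 9.51 | 99.7% |
| 20 | 0.5 | 9.59 | 90% |
| 20 | 0.8 | 9.10 | 43% |

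Dependence does not change the expected count; the differences from 1.4 and 9.5 are simulation error. It does lower the chance of at least one false positive, because false positives then come in clusters.

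**Step 4: direction.** The hypothesis predicts an increase. With a two-sided test about half of the null findings point that way: 6 / 2 = 3 for 16 channels and 56.4 / 2 = 28.2 for 48.

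**Step 5: what Tukey's test covers.** It adjusts comparisons of means within one ANOVA. If each connection has its own ANOVA, nothing in the stated plan adjusts across them.

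**Step 6: outcome against hypothesis.** The hypothesis needs each measured area labelled as damaged or normal. The outcome definition has no such label, and the eligibility criteria do not make channel position stand in for it.

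**The case against.** The strongest reply is that the article never says each connection will be tested. A mean r, a region-level r or a graph metric fits its words as well, and the network work is partly worded as exploration. This stands. A reader might infer that the whole matrix will be tested at 0.05 per entry. That is the literal result of sending a matrix-valued outcome to the stated ANOVA, but it is not explicit, so the counts above are conditional. They also rest on an assumed N, and with four regions fewer than one false positive is expected.

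Three further inferences go beyond the documents.

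- **That false connectivity findings are almost certain.** This depends on N and on dependence; at N = 20 and ρ = 0.8 the chance of any is 43%. Some false findings would also point the wrong way or lie outside the hypothesised areas.
- **That ANOVA on untransformed r is invalid.** The article mentions no transform, but a condensed article may leave that to a fuller plan. With no effect, both groups share the same distribution of r for a given connection, so the boundedness of r does not by itself inflate a between-group test.
- **That the mechanism hypothesis cannot be judged.** It has a direction and a broad location. What it lacks is a pre-named quantity to confirm or refute it.

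It can also be said that wording the hypothesis by damaged and normal areas presupposes labelling by lesion, and that multiplicity rules for secondary outcomes usually sit in the analysis plan. Both are fair. But what the outcome is belongs in the protocol, and here the stated definition is by channel and region. The exploratory wording also conflicts with listing r as a secondary outcome, with directional hypotheses and with the common significance rule.

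**Conclusion.** The point holds in a limited form. The secondary outcome r is not reduced to a per-patient endpoint, the stated 0.05 rule with Tukey's test gives no control across connections, and the outcome is not referenced to the lesion although the hypothesis is.

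If connections are tested separately, about 0.05 × N(N−1)/2 false positives are expected per comparison: 0.3, 6 and 56 for an assumed 4 regions, 16 channels and 48 channels. These figures assume one test per connection and no true effect. Dependence lowers the chance of at least one but not the expected count.

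The primary efficacy comparison on the Fugl-Meyer score is not affected. What is at stake is how far the connectivity result can support the mechanistic claim.

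**What to change.** Before the data are locked for analysis:

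1. Code each channel or region as ipsilesional or contralesional. The CT or MRI required at inclusion should show the side.
2. Pre-name one or two connectivity summaries per patient that match the Background hypothesis. Examples are mean connectivity within the ipsilesional hemisphere and mean connectivity between hemispheres, preferably averaged after Fisher's z transform. A hemisphere only approximates a damaged area, so a lesion-based region set would be closer if imaging permits.
3. Compare the groups on these summaries with adjustment for baseline at one named main time point, for example 3 weeks, and report the other time point as supportive. With two summaries use Holm: the smaller P against 0.025, then the larger against 0.05.
4. Use the same summaries for the predicted relation between r and the primary outcome.
5. Label all other channel-pair, region-pair and graph results exploratory, with false-discovery control at 5%.

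The cost is revised analysis wording and slightly more programming, with no new data collection. Fewer connections will be declared significant.
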